# Study procedures

## Management of participants in OPD

The patients will be screened in out patient department (Appendix 9)

All patients will be enrolled in the cohort during the open hours of the study clinic; the staff should consider that the 2nd intake of Coartem® has to be administered at least 8 hours after the first one.

If a patient has already been recruited for a previous episode, he will be seen by a person informed on the study and treated by the same study drug than previously.

## Visit schedule

### Inclusion visit: D0

The following tests will be carried out:

- Physical examination, collection of medical history, concomitant treatments and demographic data (age, sex), together with body weight and height,
- Vital signs: blood pressure, respiratory and pulse rates at rest, axillary temperature
- Clinical signs and symptoms
- Haematological and biochemical analyses
- Thick and thin smear and filter paper blood spot samples
- Treatment administration
- For 2nd and following attacks:
- Delivery of treatments and patient booklet
- Filter paper blood spot sample for potential DSAQ / L dosage

### Visits on D1 and D2, and D3 for the 1st attack

- Physical examination
- Axillary temperature
- Clinical safety
- Thick and thin smear
- On D1 and D2: Treatment administration
- On D3: filter paper blood spot sample for eventual DSAQ or Lumefantrine dosage.
- On D3: Hg dosage.
- Concomitant treatments
- Adverse events

### Visit on D3 for the repeat attacks

- Physical examination
- Axillary temperature
- Clinical safety
- Hg dosage.
- Thick and thin smear
- Collection and check of returned treatment and patient booklet
- Filter paper blood spot sample for eventual DSAQ or Lumefantrine dosage.
- Concomitant treatments
- Adverse events

### Post-treatment follow-up visits on D7 (+/-1), D14 (+/-1), D21 (+/- 1), D28 (+/- 2) and end-of-study visit on D42 (+/- 2)

- Physical examination
- Axillary temperature
- Clinical safety
- Haematological and biochemical analyses on D7 and D14 (if abnormal results are obtained on D7, except for Hg systematically dosed on D14) on D28 and D42 (if abnormal results are obtained on D28);
- Filter paper blood spot sample for eventual DSAQ or L dosage on D7 only
- Thick and thin smear (and filter paper blood spot samples for eventual PCR)
- Concomitant treatments
- Adverse events

In the event of a positive thick film, a PCR analysis will be carried out on the corresponding blood spot sample.

If a patient cannot perform one visit all efforts will be made to review him/her at the next visit.

## Routine visits

Patients who have not reported to the clinic for any consecutive 30-day period will be visited at home. Patients will be asked about visits to outside health facilities and the use of any medications outside the study protocol. The study protocol will be reinforced with discussion regarding the need to come to the study clinic promptly with the onset of any illness and to avoid use of outside medications. All visits will be recorded in a study registry.

## After hours visits

Study participants will be encouraged to visit Nagongera Health Centre IV outpatients department (OPD), which is adjacent to the study clinic, when urgent care is needed outside of study clinic hours. Participants will be instructed to inform health workers at OPD of their involvement in the study at the time of registration and to visit the study clinic on the following day. An updated list of patients included in the study will be provided to OPD. Identified OPD personnel will be educated about the study protocol and a nurse, employed by the project, will oversee adherence to the study protocol.

If a patient is diagnosed with uncomplicated malaria and has already been assigned a treatment regimen, he/she will receive treatment from an OPD supply of study medications based on a treatment allocation list maintained in the OPD, the data required to fill in the 1st visit of the CRF, should be collected. If a patient is diagnosed with severe malaria, he/she will receive quinine following standard treatment guidelines of both the health facility and this protocol. In these cases the OPD health workers will call one investigator to inform him about the new episode of malaria.

Patients with non-malarial illnesses will be managed at the discretion of the OPD staff. Upon discharge from the OPD, patients will receive follow-up at the study clinic as outlined in the figure. Study personnel will visit the OPD daily to inquire about visits from study patients and facilitate follow-up in the study clinic. The date and reason of all visits will be recorded in a study registry.

## Medical care outside of the study clinic

We will provide all routine medical care, including evaluations, medications available in our clinic, and cost of any transportation free of charge. In addition, we will reimburse the cost of consultation for referrals made by study physicians to other clinics and services within Nagongera Health Centre IV or Tororo Hospital. However, reimbursement of all diagnostic tests and treatment recommended outside the study clinic cannot be guaranteed in all circumstances. Decisions on reimbursement will be made by the study coordinator and the investigators, in conjunction with the sponsor if necessary.

## Definition of source data

Concomitant diseases together with any concomitant medication will be recorded directly in the case report form (CRF) after the interview with the parent.

Clinical signs and the results obtained for vital signs may be recorded directly in the case report form after the tests.

The visit dates, demographic data will be recorded in the health centre registry or in the patient’s source medical file, together with the history of fever (if applicable), the thick film results, any onset of adverse events and any new treatments taken. The printouts for the laboratory test results will be filed with the CRF, if the printouts are on thermal paper a copy of the results will be done and the document will be validated/ signed by the person responsible of laboratory tests.

Treatment accounts will be recorded directly on the sheet provided for that purpose.

A copy of the results of PCR determinations will be filed.

# Statistical considerations

## Statistical and analytical plans

The material of [Section 14](#_Ref99339812) of the Clinical Trial Protocol is the basis for the Statistical Analysis Plan for the study. This plan may be revised during the study to accommodate Clinical Trial Protocol amendments and to make changes to adapt to unexpected issues in study execution and data that affect planned analysis. These revisions will be based on blinded review of the study and data, and a final plan will be issued before database lock.

## Determination of sample size

The main analysis will be based on the non–inferiority testing of Coarsucam® (fixed dose combination of artesunate plus amodiaquine) versus Coartem® (artemether plus lumefantrine) for the first attack (supervised intakes).

The acceptable non-inferiority margin () in proportion of success between Coarsucam® and Coartem®, has been chosen at 5 %.

The test of non inferiority between Coarsucam® group and Coartem® group will be based on the unilateral confidence interval method with =5%, and  =20%,

According to Mutabingwa (7) failure rate at D28 is about 2.7% for Coartem ® (97% of successes) in East Africa (Tanzania).

With these hypotheses (computed with Nquery advisor Software, process PTE1a-1) 174 patients are needed by group of treatment.

Finally 200 patients will be included in each group in order to take account of 15% of prematurely withdrawal.

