| EVALUATION CRITERIA | - PCR corrected and uncorrected clinical and parasitological cure rate at D28 and D42 ( WHO classification) - Fever and parasitological clearance (for the 1st attack) by measuring the axillary temperature and monitoring parasitemia - Proportion of afebrile patients at D3 and proportion of patients without parasites at D3 (for following attacks) - Clinical efficacy : evolution of baseline symptoms (all clinical symptoms will be graded) - Compliance based on number of residual tablets in blisters - Treatment incidence density during the 2 years of follow up (comparison of the number of malaria attacks between the two arms during the 2 years) - Mean delay between 2 attacks during the 2 years of follow up - Clinical tolerability ( incidence and intensity of recorded AE ) - Biological tolerability (Hb, Bilirubin, ALAT, Creatinine, Leukocytes, Neutrophils, and Platelets count) |
| RESCUE TREATMENT | Because PCR will not be available in real time:  Any failure before D14, will be considered as a recrudescence and will receive rescue treatment  Failure at D14 or later will be considered as reinfection; and the same ACT treatment will be repeated |
| ASSESSMENT SCHEDULE | Refer to flowchart |
| STATISTICAL CONSIDERATIONS | **Number of patients:**  With a non-inferiority margin () chosen at 5 %, =5%, and  =20%, and the hypothesis of 97% of success rate with Coartem®, 174 patients are requested; taking account of 15% of lost follow-up 200 patients are needed per treatment group.  **Statistical generalities**  All statistical analyses will be performed on SAS software (version 8.2 for PC).  All statistical tests will be bilateral and performed at a 5% significance level excepted for the non-inferiority analysis (unilateral confidence interval)  **Efficacy Analysis**  The non-inferiority of PCR adjusted adequate clinical and parasitological response at D28 (WHO protocol in vivo D28 2003) of Coarsucam® (artesunate plus amodiaquine) versus Coartem® (artemether plus lumefantrine), based on the first malaria attack of each patient will be studied using the 95% one-sided confidence interval on ITT and Per Protocol populations. |
| DURATION OF STUDY PERIOD | 2 years  Each attack will be actively followed for 42 days |

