#### Analysis of primary efficacy variable(s)

The main criterion is defined as the response to the treatment after PCR correction according to WHO guidelines 2003 for the first attack.

The response will be classified such as:

- ETF (Early Treatment Failure)
- LPF ( Late Parasitological Failure)
- LCF (Late Clinical Failure)
- ACPR (Adequate Clinical and Parasitological Response)

The proportion of successes will be compared by group of treatment.

The main analysis is strictly defined as the non-inferiority analysis for the first attack.

The test of non inferiority between Coarsucam® group and Coartem® group will be based on the confidence interval method: the lower limit of the 95% one-sided confidence interval for the proportion difference between the two treatment groups should be greater than - to conclude non-inferiority.

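### Enrolling 200 per arm leaves 170 evaluable after the stated 15% loss, 4 fewer than the 174 the protocol says it needs; 200 covers a 13% loss (minor).

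*Protocol*

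**What the plan says.** Protocol section 14.2 (Determination of sample size) gives the requirement for the primary non-inferiority comparison on the first attack: "174 patients are needed by group of treatment". It then sets enrolment: "Finally 200 patients will be included in each group in order to take account of 15% of prematurely withdrawal".

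The synopsis (section 1, Statistical considerations) gives the same figures, calling the loss a loss to follow-up: "174 patients are requested; taking account of 15% of lost follow-up 200 patients are needed per treatment group".

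The design inputs are a one-sided 5% level, 80% power, a margin of 5 percentage points, and a comparator rate described as "failure rate at D28 is about 2.7% for Coartem ® (97% of successes) in East Africa (Tanzania". Section 14.5.3.1 bases the conclusion on "the lower limit of the 95% one-sided confidence interval for the proportion difference between the two treatment groups". Neither place shows how the step from 174 to 200 was made.

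**The concern.** When a fixed share of enrolled patients is expected to drop out, the evaluable requirement has to be divided by the share retained. Multiplying it by one plus the loss gives too small a number. Here the enrolled figure, reduced by the protocol's own loss rate, does not return the protocol's own requirement.

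What is at stake is the accuracy of the sample size statement for the primary test. Section 14.1 makes section 14 the basis of the statistical analysis plan, so the mismatch could be carried forward.

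**Working it through.** **Inputs.** 174 needed, 15% loss and 200 enrolled per arm (section 14.2 and synopsis). The 174 is taken as given.

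**Reproducing the 200.** 174 x 1.15 = 200.1, which matches the stated 200. Division does not: 174 / (1 - 0.15) = 204.7, so 205.

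**Evaluable patients at the stated loss.** 200 x 0.85 = 170. Shortfall: 174 - 170 = 4 per arm, or 4 / 174 = 2.3%.

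**Loss that 200 can absorb.** 1 - 174 / 200 = 0.13, that is 13%. Check: 200 x 0.87 = 174.

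**Enrolment that would keep 174 at 15% loss.** 205 per arm, 410 in total. Check: 205 x 0.85 = 174.25. This is 5 per arm more than planned.

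**Effect on power.** The settings are a one-sided 5% level, a 5-point margin and equal true success in both arms. The protocol names no other rate for the test arm, so equality is an assumption. Both 97% and 97.3% (1 - 0.027) are shown. The protocol does not name the type of interval, so several are shown.

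- Exact power sums the binomial probabilities of all outcome pairs whose lower limit exceeds -0.05.
- Wald lower limit: d - 1.645 x sqrt[p1(1-p1)/n + p2(1-p2)/n].
- Newcombe lower limit: d - sqrt[(p1 - l1)^2 + (u2 - p2)^2], with l1 and u2 the Wilson limits at z = 1.645.
- Farrington-Manning approximation: power = Phi[(0.05 x sqrt(n) - 1.645 x s0) / s1], with s0 from the constrained estimates and s1 = sqrt[2p(1-p)].

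| Method | Success | n = 174 | n = 170 | Change, before rounding (points) |
| --- | --- | --- | --- | --- |
| Newcombe, exact | 97% | 81.7% | 79.3% | 2.5 |
| Newcombe, exact | 97.3% | 84.4% | 82.1% | 2.3 |
| Wald, exact | 97% | 85.9% | 85.3% | 0.6 |
| Wald, exact | 97.3% | 88.8% | 87.8% | 1.0 |
| Farrington-Manning, approximate | 97% | 78.1% | 77.1% | 0.9 |
| Farrington-Manning, approximate | 97.3% | 80.7% | 79.8% | 0.9 |

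Exact power moves in steps. With Newcombe at 97% it is already 80.0% at n = 172, so part of the 2.5-point change is discreteness.

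**The case against.** The strongest reply is that the gap is too small to matter: 5 enrolled or 4 evaluable patients per arm, in a calculation whose inputs are themselves rounded. That stands as to size. It does not make the three figures agree.

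A second reply is that the shortfall does not apply to both primary analysis sets. This also largely stands. Section 14.4.1 makes completed treatment and completed assessments a condition of the Per Protocol set only. The ITT set keeps dosed patients except those with double rejection or vomiting at the first intake. Section 12.2 leaves the handling of patients lost for the primary endpoint to the statistical analysis plan, which is not at hand. The 170 is therefore a Per Protocol or complete-case count, and the documents do not show that ITT loses 15%.

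A third reply is that multiplication is only inferred. That is fair. No inflation formula is given, and the 200 may have been reached in another way, for example as a convenient round number. The mismatch does not depend on the cause.

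Two stronger readings are tempting, and neither is supported:

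- **That the design does not deliver its stated 80% power.** At n = 170, only one of the four exact combinations above falls below 80%, by 0.7 points. The Farrington-Manning figure at 97% is below 80% at 174 as well, so the missing 4 patients do not cause that. The protocol fixes neither the interval type nor a single unrounded rate that would settle the matter.
- **That the base figure of 174 is itself wrong or untraceable.** A failure rate of about 2.7% written as 97% success is ordinary rounding. Section 14.2 names the software and procedure, and the choice of interval method is commonly left to the analysis plan. Farrington-Manning gives 171 at 97.3% and 175 at 97.2%, so 174 is plausible.

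**Conclusion.** Wrong as written, and minor. At the stated 15% loss, 200 per arm leaves 170 evaluable, 4 below the stated requirement; 200 is sufficient for a 13% loss. The conclusion rests only on reading the 15% as a share of those enrolled, which is the natural sense of both statements.

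The cost is roughly 1 to 2.5 points of power (0.6 at the smallest) in a set that actually loses 15%. Exact power at 170 is 79.3% to 82.1% with Newcombe and 85.3% to 87.8% with Wald, assuming equal success in the two arms. This is not evidence of a materially underpowered trial.

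**What to change.** Correct the sentence in section 14.2 and its counterpart in the synopsis, in one of two ways:

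- State that 200 per arm allows for 13% loss and leaves 174 evaluable.
- Keep the 15%, state that 200 per arm leaves 170 evaluable, and give the power for 170 recalculated with the procedure that produced the 174.

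Use the same wording and the same term for the loss in both places. The cost is one sentence in each and, for the second option, one rerun of the power calculation. No extra patients and no change to the design are needed.

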## Analysis variables

### Demographic and baseline characteristics

The demographic data and parameters recorded on inclusion will undergo a descriptive analysis according to treatment groups on the safety population.

The evaluations used as baseline values will be the last evaluations performed before treatment administration. Any repeated evaluations will be considered baseline values if performed prior to the first intake of treatment.

### Efficacy variables

#### Primary efficacy variable

The main criterion is defined as the adequate response to the treatment at D28, after PCR correction according to WHO guidelines for assessing response to treatment (2003), for the first attack and for both treatment groups.

#### Secondary efficacy variables

Comparison of both treatment groups in terms of:

- Response to treatment at D28, before PCR correction for the first attack
- Response to treatment at D28, before and after PCR correction for all repeated attacks
- Response to treatment at D42, before and after PCR for each attack
- Time to parasite clearance (proportion of aparasitaemic patients at 24, 48 and 72 hours) for the first attack
- Time to fever clearance (proportion of afebrile patients at 24, 48 and 72 hours) for the first attack
- Proportion of afebrile patients at D3 for the following attacks
- Proportion of patients without parasite at D3 for the following attacks
- Evolution of number of gametocytes carriers during the 42 days of follow-up and for each episode
- Evolution of the mean of gametocytes during the 42 days of follow-up and for each episode
- Evolution of abnormal biological baseline value for each attack
- Number of malaria attacks during the 2 years of follow up (treatment density)
- Evolution of the average duration between 2 attacks during the 2 years of follow up
- Evolution of haemoglobin value for each patient during each attack (between D0 and D28) during the 2 years of follow up
- Evolution of mean haemoglobin values at D0,D3, D7,D14 and D28 for each episode during the 2 years of follow up
- Evolution of Hackett score during the 2 years of follow-up

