### Inclusion criteria for each attack (except the failures)

- Body weight ≥ 5 kg
- Able to be treated by oral route
- Fever (axillary temperature ≥ 37.5 degrees Celsius) at D0 or history of fever within the previous 24 hours (this criteria is not required in case of late failure after D14 in the previous attack)
- confirmed *Plasmodium falciparum* infection with positive parasitemia
- Haemoglobin value ≥ 5.0 g/dl;
- Agreement to comply with the study protocol

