### Secondary criteria

For the first episode:

- Clinical and parasitological efficacy is defined by grading clinical signs further to an interview by the investigator, together with the values obtained for temperature and parasitaemia before and after PCR correction at D42, and before PCR correction at D28
- Monitoring of parasitaemia during the different visits in order to define clearance
- Measure of axillary temperature at each visit in order to define the clearance of fever
- Monitoring of gametocytaemia during each evaluation

For the following episodes:

- Clinical and parasitological effectiveness is defined by grading the clinical signs further to an interview by the investigator, together with the values obtained for temperature and parasitaemia before and after PCR correction at D28 and D42
- Proportion of patients without fever at D3 obtained with the values of temperature (axillary temperature<37.5°C)
- Proportion of patients without parasites at D3 (negative thick smear)

During the total follow up of the cohort:

- Compare the number of malaria attack for each patient between two arms and mean delay between 2 attacks during the 2-years of follow up
- Compare the number of patients with anemia at D0 of each episode during the 2 years per arm.
- Compare the evolution of anaemia by patient between D0 and D28 for each episode

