#### Analysis of secondary efficacy variables

Non inferiority analysis will be performed on the same way than for the main criterion for

- before PCR corrected cure rate at D28 for the first attack
- before and after PCR corrected cure rate at D28 for the following attacks
- before and after PCR corrected cure rate at D42 for all attacks

An analysis for repeated measurements will be performed. A model will be built in order to explain the success/failure of the response. The rank of the attack, the group of treatment and their interaction will be included in the model. Some other relevant parameters could be included if descriptive analysis find out discriminating items.

Comparison between treatment groups will be provided for the following parameters

- Time to parasitological clearance for the 1st episode (number of patients without parasite from D1 to D3)
- Time to fever clearance for the 1st episode (number of patients without temperature from D1 to D3)
- Proportion of patients without fever at D3 for repeated attacks
- Proportion of patients without parasite at D3 for repeated attacks
- Evolution of number of gametocyte carriers and mean values of gametocyte rate during the 42 days of follow-up for each episode
- Evolution of hemoglobin value for each patient during each attack (between D0 and D28) occurring during the 2 years of follow up
- Evolution of mean hemoglobin values at D0,D3, D7,D14 and D28 of each episode during the 2 years of follow up
- Evolution of Hackett score during the 2 years of follow up

The number of malaria attacks will be summarized by treatment group and overall.

The evolution of average duration between 2 attacks during the 2 years of follow up will be computed and analyzed using survival analysis methods.

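### Fever clearance (attack 1) and afebrile status at D3 (repeat attacks) ignore D0 temperature, which dilutes the first comparison and can distort the second by a small amount

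*Protocol*

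**What the plan says.** Protocol section 14.3.2.2 (Secondary efficacy variables) lists "Time to fever clearance (proportion of afebrile patients at 24, 48 and 72 hours) for the first attack" and, for repeat attacks, "Proportion of afebrile patients at D3 for the following attacks". Section 14.5.3.2 restates the first as "Time to fever clearance for the 1st episode (number of patients without temperature from D1 to D3" and the second as "Proportion of patients without fever at D3 for repeated attacks". Section 10.1.2 gives the only explicit cut-off, for repeat attacks: "Proportion of patients without fever at D3 obtained with the values of temperature (axillary temperature<37.5°C".

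Section 14.5.3 analyses efficacy on the ITT and per-protocol populations. Section 14.4.1 defines ITT as included patients with at least one dose, less those with double vomiting or rejection at the first intake, and per protocol as its compliant subset. Neither set depends on temperature at D0.

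The entry rule for each attack (section 8.2.2) is "Fever (axillary temperature ≥ 37.5 degrees Celsius) at D0 or history of fever within the previous 24 hours". The same bullet waives the criterion for an attack that follows a late failure beyond D14. Under section 9.7.4, failures on D14 or later are handled as reinfections and receive the allocated drug again. Appendix 1 defines late parasitological failure as parasitaemia with temperature below 37.5 °C.

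**The concern.** A child with a D0 temperature below the cut-off can be counted as afebrile on D1, D2 or D3 without any measured fever having resolved. The variable in attack 1 is named fever clearance, and parasitological and fever clearance is a stated secondary objective (section 6.2). A proportion that includes such children answers a different question.

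The consequence differs between the two settings. In attack 1 the share afebrile at D0 is a baseline feature, balanced by randomisation in expectation, so the risk is a difference that looks smaller than it is. In repeat attacks an afebrile late parasitological failure can open the next attack. The share of attacks that start afebrile then depends partly on how each drug performed earlier, and can differ by arm for reasons unrelated to fever clearance. The arm with more afebrile late failures would gain on the D3 fever endpoint.

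**Working it through.** The protocol states no expected value for either fever endpoint, so there is no figure to reproduce. The inputs from the protocol are 200 children per arm (section 14.2) and two-sided 5% tests for secondary comparisons (section 14.5). The share afebrile at D0 and the clearance rates are not given. Those used below are assumptions shown over a range.

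**Attack 1.** Let *f* be the share afebrile at D0, *c* the proportion of febrile-at-D0 children who are afebrile at the time point, and *s* the same proportion among children afebrile at D0. For each arm

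P = f·s + (1 − f)·c,

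and the difference between arms is f·(s₂ − s₁) + (1 − f)·(c₂ − c₁). If *s* is the same in both arms, as it nearly is when these children mostly stay afebrile (s close to 1), the difference is (1 − f)·(c₂ − c₁). For c₂ − c₁ = 10 points:

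- f = 20%: 0.80 × 10 = 8 points
- f = 40%: 0.60 × 10 = 6 points
- f = 60%: 0.40 × 10 = 4 points

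Power (normal approximation, pooled variance under the null, s = 1), with 200 per arm for all children and 200·(1 − f) per arm for the febrile-at-D0 subset:

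| Clearance if febrile at D0 | f | Difference, all children | Power, all | Power, febrile only |
|---|---|---|---|---|
| 60% v 75% | 20% | 12 points | 0.78 | 0.82 |
| | 40% | 9 points | 0.62 | 0.70 |
| | 60% | 6 points | 0.43 | 0.53 |
| 80% v 90% | 20% | 8 points | 0.69 | 0.71 |
| | 40% | 6 points | 0.56 | 0.58 |
| | 60% | 4 points | 0.39 | 0.42 |
| 92% v 97% | 20% | 4 points | 0.50 | 0.50 |
| | 40% | 3 points | 0.39 | 0.40 |
| | 60% | 2 points | 0.28 | 0.28 |

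Restricting the denominator mainly restores the size of the estimate. It also gains power when residual fever is common, but almost none once clearance exceeds about 90%.

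**Repeat attacks.** Suppose true clearance *c* is identical in both arms and only the afebrile-at-entry shares differ, f_A and f_B. With s = 1 the spurious difference is

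(f_B − f_A)·(1 − c).

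For shares of 20% and 40%:

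- c = 90%: 0.20 + 0.80 × 0.90 = 92% against 0.40 + 0.60 × 0.90 = 94%, which is 2 points
- c = 95%: 0.20 + 0.80 × 0.95 = 96% against 0.40 + 0.60 × 0.95 = 97%, which is 1 point
- c = 80%: 0.20 × 0.20 = 4 points

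A more extreme split of 10% against 50% gives 8, 4 or 2 points at 80, 90 or 95% clearance. A mild split of 10% against 20% at 95% gives 0.5 points. If some afebrile entrants become febrile (s below 1 but above *c*, equal in both arms), the factor (1 − c) becomes (s − c) and the spurious difference is smaller. Restricting to attacks febrile at D0 makes it zero in this model.

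**The case against.** The protocol nowhere says that all children form the denominator. That reading combines short variable names with the general ITT and per-protocol rule, and an analysis plan not seen here could narrow it. This stands only in part. The variables, the analysis sets and, for repeat attacks, the cut-off are all stated without condition, and section 14.1 makes section 14 the basis for the analysis plan.

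A child who enters attack 1 on history alone was reported febrile within the previous 24 hours, may have had paracetamol (section 9.7.2 allows it and records earlier use), and may be febrile again on D1 to D3. Such a child would count against the drug, and restriction would drop that information. This stands. It makes the shrinkage factor approximate, and it is a reason to keep the all-patient figure in the report.

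For repeat attacks the variable is named as a status at D3, not as clearance. Appendix 1 also uses D3 temperature, with parasitaemia, to define early failure whatever the D0 reading. As a description, the all-patient proportion is therefore legitimate.

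A reader might infer that the attack-1 comparison is biased, or that the repeat-attack endpoint will favour the less effective drug. The documents support neither. Attack 1 is compared as randomised. The protocol gives no afebrile share by arm, so a distortion in repeat attacks is possible but not shown. Nor does restriction yield a clean randomised comparison there: who has a repeat attack, and whether that child is febrile at its D0, both arise after randomisation.

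**Conclusion.** The point holds in a limited form. As written, both fever endpoints include children with no measured fever at D0, and in repeat attacks some with no fever required at all. The attack-1 effect is dilution by roughly (1 − share afebrile at D0), provided those children mostly stay afebrile. In repeat attacks a spurious difference can arise, about 1 to 2 points for a 20-point split in afebrile-at-entry share at 90 to 95% clearance, and larger only if residual fever at D3 is common or the split more extreme. Every share and clearance rate behind these figures is an assumption. Only secondary endpoints are involved, the primary PCR-adjusted D28 response is unaffected, and the priority is low.

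**What to change.** In sections 14.3.2.2 and 14.5.3.2, state that the main comparisons of fever clearance (attack 1) and of the proportion afebrile at D3 (repeat attacks) are made among attacks with axillary temperature of at least 37.5 °C at D0 of that attack. Report the all-patient proportion alongside. Show history-only entrants and afebrile late failures as separate rows. Label the repeat-attack comparison as subject to post-randomisation selection.

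The cost is a few sentences. Axillary temperature is already measured at the D0 visit (section 13.2.1), so no data collection changes. The main comparison has a smaller denominator, for example 120 instead of 200 per arm if 40% are afebrile at D0, with little or no power gain when D3 clearance is above about 90%. The change removes the arithmetic artefact in repeat attacks but not the selection into them.
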